#### Step 2 (Table 2)

Differentiated PrEP distribution strategies are needed to optimize PrEP, especially in postpartum women who struggle to stay engaged in care. Similar to community-based ART delivery, we will test a differentiated PrEP delivery model for options for community PrEP delivery and pick up for postpartum women who want to continue on PrEP, but either discontinue, or have poor persistence in Step 1.

**Table 2 Tab2:** Study and clinic visits by intervention and standard of care arms in Step 2 of RCT in SCOPE-PP study, Cape Town, South Africa

*If PrEP discontinued, missed visit, or poor persistence (no TFV in urine) offer new randomization (RCT 2) with chance of differentiated PrEP delivery*			
	Counseling group	Community delivery group	Steps
**Baseline study visit**	In clinic: PrEP refill and counseling with urine testing and feedback	At community pick up points^a^: PrEP refill + HIV self testing for monitoring HIV status	In study site (behind clinic): • Consent to new randomization • Survey • Reimbursement
**3 month Service visit**	In clinic: PrEP refill and counseling with urine testing and feedback	At community pick up points^a^: PrEP refill + HIV self testing for monitoring HIV status	Standard monitoring • No reimbursement for time
**6 month Service visit**	In clinic: PrEP refill and counseling with urine testing and feedback	In community^a^: PrEP refill + HIV self testing for monitoring HIV status	Standard monitoring No reimbursement for time
**9 month Study visit**	In clinic: PrEP refill and counseling with urine testing and feedback	In community^a^: PrEP refill + HIV self testing for monitoring HIV status Referral to continue on PrEP at local clinic	In study site: • Blood collection • Survey • Reimbursement for time
**End of study and referral for ongoing PrEP care in clinic**			

^a^Study will offer community pick up in local church or hall, depending on participant preference

*PrEP* pre-exposure prophylaxis, *HIVST* HIV self-testing, *TFV* tenofovir diphosphate

Participants in the intervention arm who are adherent and continued on PrEP at 6 months will continue with first randomization of sustained biofeedback through to 12-months follow-up. Participants in the SOC arm who are adherent and continued on PrEP at 6 months will continue with first randomization of SOC through 12-months follow up in clinic. Meanwhile, participants who are non-adherent (per TFV urine testing) and/or discontinued PrEP at 6 months in the Step 1 study, and want to continue in the study, will be re-randomized to Step 2.

##### Recruitment and enrollment

Postpartum women who were on PrEP in Step 1 but discontinued PrEP or were not adherent to PrEP during periods of sexual activity (prevention-effective persistence) and want to continue on PrEP will receive a second randomization to receive additional services. Participants who are eligible for Step 2 will complete a second written informed consent immediately after being screened. The inclusion criteria for Step 2 are:Enrolled in Step 1 of SCOPE-PPDiscontinued PrEP (did not return for PrEP refill prescription) or were not adherent (negative urine TFV result, indicating did not take PrEP in last 48–72 hours)Want to continue taking PrEPDocumented HIV-negative at the time of Step 2 screeningStill lives within 20 km of the study facilityWithout psychiatric or medical contraindications to PrEP usePostpartum with live infant,Able and willing to consent to study participation.

Individuals not meeting the above criteria will be excluded.

##### Randomization

For Step 2, individual women will be randomized using a 1:1 ratio to either 1) persistence counseling through biofeedback and PrEP rapid collection or 2) persistence counseling, PrEP rapid collection, plus differentiated PrEP delivery (community PrEP delivery). We will use the same randomization strategy as described under Step 1.Intervention: Enhanced adherence counseling through biofeedback and rapid PrEP collection following HIVST

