**Fig. 2 Fig2:**
[figure not shown]
SCOPE-PP Study Design: Step 1 and Step 2

After enrolling in the trial and completing a baseline survey, PBFW will be assigned immediately to a study ID based on the randomization list. Study ID’s will be linked with the pre-assigned blocked randomization by the study data manager and pre-loaded into the tablet device but will be unknown to the study staff until survey and randomization modules are completed and saved, ensuring randomization cannot be manipulated by the study staff. Once finalized, the randomization results will appear on the tablet device as a picture on a pre-programmed tablet, and will be shown to the participant to maximize transparency and study buy-in.

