##### Intervention

We will randomize ~ 325 postpartum women from Step 1 who disengaged from PrEP during the first 6-months post enrollment and desire to stay on PrEP to:Intervention 1: Rapid PrEP collection following HIVST and differentiated model of community-based PrEP delivery.Intervention 2: Enhanced adherence counseling through biofeedback in the clinic and rapid PrEP collection following HIVST

**Community PrEP delivery** with HIVST and counselling at a community location (hall, library or NGO/church) will be available for women randomized to intervention 1 at a select, pre-determined date of the month. The counsellor will be available to answer questions and collect data on adherence and side effects. If randomized to differentiated care the participant will not receive enhanced biofeedback in the clinic (Intervention 2).

We will continue to assess study outcomes at study visits in the clinic on site including PrEP continuation and persistence and DBS to assess objective persistence. A summary of the Step 1 and Step 2 study design can be found in Table 3.

**Table 3 Tab3:** SCOPE-PP Step 1 and Step 2 Study populations, Intervention, Outcomes and Hypotheses

Study	Study Population	Intervention	Outcome	Hypothesis
Step 1:	*N* = 650 **pregnant** women at enrollment	Persistence biofeedback	PrEP continuation and persistence (urine TFV at 6 months postpartum & verified post hoc via DBS of TFV-DP)	Persistence biofeedback will improve PrEP continuation & persistence by > 15% compared to standard of care (no intervention) in pregnant and early postpartum women
Step 2^a^:	*N* = Approximately 325 **postpartum** women at enrollment Composed of ALL women who want to use PrEP but are struggling to engage w/PrEP from Step 1 (EARLY-PREP-P)	Differentiated PrEP delivery (in community pick up points) with HIVST (for participant and partner) Vs. Persistence biofeedback	PrEP continuation and persistence through 12-months follow up per urine TFV (post hoc DBS analysis)	In postpartum women who want to use PrEP but struggle to engage with initial use, PrEP use continues and improves by > 15% differentiated PrEP delivery (in community pick up points) at longer time periods (through 12-months follow up)

^a^Step 2 sample size is approximate because the participants will be recruited from the Step 1 and that number will depend on how many want to be in the study and how many discontinue PrEP and/or have poor persistence per urine TFV testing

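### Step 2 pools women from both Step 1 arms while one of its arms repeats the Step 1 intervention, yet Step 1 arm is not used in the described allocation or listed as a subgroup

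*Protocol article*

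**What the plan says.** Four statements in the protocol article bear on this point.

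- **Who enters Step 2.** The text after Table 2 says that women from Step 1 who are non-adherent or have discontinued at 6 months and "want to continue in the study, will be re-randomized to Step 2". Table 3 describes the Step 2 population as "Composed of ALL women who want to use PrEP but are struggling to engage w/PrEP from Step 1". The Step 2 inclusion criteria ask for enrollment in Step 1, without regard to arm.
- **How they are allocated.** The Step 2 Randomization section states: "For Step 2, individual women will be randomized using a 1:1 ratio to either" of two arms, and adds "We will use the same randomization strategy as described under Step 1". The Step 1 text describes study IDs "linked with the pre-assigned blocked randomization by the study data manager". It names no stratification factor.
- **What one arm contains.** The Step 2 Randomization section gives the first arm as "persistence counseling through biofeedback and PrEP rapid collection", and the Intervention section words it as "Enhanced adherence counseling through biofeedback in the clinic and rapid PrEP collection following HIVST". This is the package of the Step 1 intervention arm. The Intervention section also says that women allocated to community delivery do not receive the in-clinic biofeedback.
- **How effects are broken down.** The Data analysis section lists a priori subgroups: age, education, marital status, and participant and partner HIV testing history. Step 1 arm is not among them. Step 2 is described as one pooled comparison of proportions.

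**The concern.** The Step 2 comparator does not mean the same thing for every woman. For someone who had standard of care in Step 1, biofeedback counseling is new. For someone who had the Step 1 intervention, it repeats the package she was assigned when her PrEP use lapsed. It is plausible that the benefit of community delivery over counseling differs between these groups, and that their outlook in Step 2 differs whichever arm they receive.

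Two things are at stake. The first is interpretation: the pooled effect is a weighted average of two contrasts, and the weights depend on how Step 1 turns out. Whether stepping up to community delivery helps once biofeedback has not worked is answered only by the former intervention women. The article also plans a combined analysis of both steps and an integrated cost-effectiveness analysis, and a single pooled Step 2 effect may fit neither route through the trial. The second, smaller matter is precision: without stratification or adjustment, Step 1 arm can be unevenly split between the Step 2 arms by chance.

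**Working it through.** The article gives no figure on this point, so there is none to reproduce. Its Step 2 power statement (80% for a 20-point difference with about 320 women) is a separate matter. The sizes below use 160 per arm, which gives about 79% power for 30% against 45%.

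**Inputs from the article.** Expected persistence of 30% (standard of care) and 45% (intervention), 325 women per Step 1 arm, about 320 women followed in Step 2 at 1:1, two-sided alpha 0.05 (Sample size considerations; Randomization; Data analysis).

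**Inputs assumed.** Equal interest and retention in both Step 1 arms; eligibility rates that follow the 30% and 45%; a difference in Step 2 outlook between the two origins of 10 to 20 points; overall Step 2 persistence of 30% in the imbalance simulations, and 37.5% (midway between 30% and 45%) for the interaction.

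**1. Mix of the Step 2 pool.**
- Former standard of care: 325 × 0.70 = 227.5
- Former intervention: 325 × 0.55 = 178.75
- Share former intervention: 178.75 / 406.25 = 0.44, leaving 0.56 former standard of care.

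The share does not depend on the number enrolled, but it does depend on the Step 1 result. If Step 1 shows no difference it is 0.50. With the pilot's urine figures (60% against 17%) it is 0.40 / (0.40 + 0.83) = 0.33.

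**2. What pooling can conceal (illustration only).** Suppose the true Step 2 effects are 25 points in former intervention women and 7 points in former standard-of-care women. The pooled effect is 0.44 × 25 + 0.56 × 7 = 14.9 points, close to the hypothesized 15. With a share of 0.50 the same two effects give 16.0; with 0.33 they give 0.33 × 25 + 0.67 × 7 = 12.9.

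**3. Chance imbalance without stratification.**
- SD of the between-arm difference in share: √(0.44 × 0.56 × 2/160) = 0.0555.
- 95% range: 1.96 × 0.0555 = 0.109. Simulation with 320 women gives SD 5.6 points, with 95% of allocations within about 10.6 points, and is nearly the same for blocks of 4 or 8.

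The shift in the Step 2 estimate is this imbalance times the difference in outlook:

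| Assumed difference in outlook | SD of shift | 95% of shifts within |
|---|---|---|
| 10 points | 0.0555 × 10 = 0.6 points | 0.109 × 10 = 1.1 points |
| 20 points | 0.0555 × 20 = 1.1 points | 0.109 × 20 = 2.2 points |

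The sampling standard error of the Step 2 difference is about 5.1 to 5.4 points, so the shift is small beside it.

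**4. Error rates (40,000 simulated trials, 20-point difference in outlook).** Type I error without stratification is 4.9%. Power for a 15-point effect is 78.7% unstratified and 79.6% stratified, a gain of 0.9 points.

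**5. Precision of the interaction.** At 44% of 160, each Step 2 arm has about 70 former intervention and 90 former standard-of-care women. With persistence of 37.5%, SE = √[2 × 0.375 × 0.625 × (1/70 + 1/90)] = √0.0119 = 0.109, or about 11 points. The 95% CI half-width is 1.96 × 10.9 = 21 points. For the 18-point difference in step 2, 18/10.9 = 1.65, so power is about P(Z > 1.96 − 1.65) = 38%.

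**The case against.** The strongest case on the other side has four parts.

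*The article is condensed.* It gives no block size or list structure, and it mentions an adjusted model without naming the covariates. An unseen full protocol or SAP may stratify or adjust. This stands as a limit: the documents do not show that Step 1 arm goes unused in the Step 2 analysis. But the article does state the allocation method by carrying over a Step 1 scheme, and that scheme could not itself have used Step 1 arm as a stratum. It also states the subgroup list. Both can be improved as written.

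*Pooling is deliberate.* Table 3 defines the population as everyone who struggles with PrEP, and the trial calls itself pragmatic. The average effect in that population is a legitimate target. This stands, and is why the pooled effect should remain primary.

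*Not every former intervention woman has had the package and failed on it.* Some qualify because they did not return for a refill and may have had little biofeedback, and rapid collection is in both Step 2 arms. This stands in part. It makes the contrast between origins less sharp without removing it.

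*Effects by origin will be imprecise.* This stands, with an interaction SE of about 11 points. It argues for an exploratory label and a confidence interval, not for omitting the estimate.

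A reader might also infer that unstratified allocation biases the Step 2 comparison, or that Step 1 arm is a known, strong prognostic factor. The documents support neither. Randomization balances Step 1 arm in expectation, and no section reports later persistence by earlier arm.

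**Conclusion.** The point holds as a matter of interpretation and modest efficiency, not of validity. On the plan's own rates, and assuming equal interest and retention, the pooled Step 2 effect combines about 56% new biofeedback against community delivery with about 44% repeat biofeedback against community delivery. Step 1 arm is a plausible effect modifier and prognostic factor; the described allocation does not use it and the subgroup list omits it. Chance imbalance would typically shift the estimate by about 1 point, and by up to about 2 points if the two origins differ by an assumed 20 points. Type I error is held and stratifying gains about 1 point of power. The size of any effect modification cannot be derived from the documents; the 25- and 7-point effects only illustrate how it could be hidden. An unseen SAP may already adjust for Step 1 arm, which would settle the imbalance but would not by itself show the effect by origin.

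**What to change.** 1. Stratify the Step 2 list by Step 1 arm, with one blocked list per origin. If Step 2 allocation has begun, adjust for Step 1 arm in the Step 2 primary model instead.
2. Add Step 1 arm to the prespecified subgroups for Step 2.
3. Report the Step 2 effect by Step 1 arm, with the interaction estimate and its 95% CI. State beforehand that this is exploratory and imprecise (SE about 11 points at about 320 women).
4. Keep the pooled effect as the primary result, and report the share of women from each Step 1 arm beside it.

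Stratification or adjustment alone deals only with imbalance; items 2 and 3 address the mixture of contrasts. The cost is one extra list in the tablet program or one covariate, plus one low-powered subgroup estimate that must not be over-read. No extra participants or visits are needed.

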##### Intervention

We will randomize ~ 325 postpartum women from Step 1 who disengaged from PrEP during the first 6-months post enrollment and desire to stay on PrEP to:Intervention 1: Rapid PrEP collection following HIVST and differentiated model of community-based PrEP delivery.Intervention 2: Enhanced adherence counseling through biofeedback in the clinic and rapid PrEP collection following HIVST

**Community PrEP delivery** with HIVST and counselling at a community location (hall, library or NGO/church) will be available for women randomized to intervention 1 at a select, pre-determined date of the month. The counsellor will be available to answer questions and collect data on adherence and side effects. If randomized to differentiated care the participant will not receive enhanced biofeedback in the clinic (Intervention 2).

We will continue to assess study outcomes at study visits in the clinic on site including PrEP continuation and persistence and DBS to assess objective persistence. A summary of the Step 1 and Step 2 study design can be found in Table 3.

**Table 3 Tab3:** SCOPE-PP Step 1 and Step 2 Study populations, Intervention, Outcomes and Hypotheses

Study	Study Population	Intervention	Outcome	Hypothesis
Step 1:	*N* = 650 **pregnant** women at enrollment	Persistence biofeedback	PrEP continuation and persistence (urine TFV at 6 months postpartum & verified post hoc via DBS of TFV-DP)	Persistence biofeedback will improve PrEP continuation & persistence by > 15% compared to standard of care (no intervention) in pregnant and early postpartum women
Step 2^a^:	*N* = Approximately 325 **postpartum** women at enrollment Composed of ALL women who want to use PrEP but are struggling to engage w/PrEP from Step 1 (EARLY-PREP-P)	Differentiated PrEP delivery (in community pick up points) with HIVST (for participant and partner) Vs. Persistence biofeedback	PrEP continuation and persistence through 12-months follow up per urine TFV (post hoc DBS analysis)	In postpartum women who want to use PrEP but struggle to engage with initial use, PrEP use continues and improves by > 15% differentiated PrEP delivery (in community pick up points) at longer time periods (through 12-months follow up)

^a^Step 2 sample size is approximate because the participants will be recruited from the Step 1 and that number will depend on how many want to be in the study and how many discontinue PrEP and/or have poor persistence per urine TFV testing

### Data collection

Participants who enroll in Step 2 will complete another survey immediately following enrollment. This survey will assess prior PrEP persistence (barriers and facilitators), HIV risk (including sexual activity, partner HIV status and risk perception), prior use of PrEP or attitudes about PrEP, and information on IPV and substance use. All surveys will be conducted in the local language by trained study staff using electronic tablets with REDCap software.

### Follow-up data

Similar to Step 1, participants will complete a follow-up survey every 3 months (4 follow-up surveys total). Surveys will ask about HIV risk, sexual activity and PrEP persistence, and perceptions about differentiated care (if received). Any adverse events, side effects and IPV will be recorded at each visit. Participants who report substance use, violence and/or IPV will be referred to a local NGO for social services and counseling.

### Outcomes

The primary outcome for Step 2 is continued PrEP use and persistence in later postpartum. PrEP continuation and persistence 6 months after the second randomization, (~ 12-months follow up) per urine TFV (post hoc DBS analysis) comparing enhanced counseling alone to the SOC arm. Secondary outcomes are the same as Step 1 and include: perfect PrEP persistence during Step 2, HIV incidence during Step 2, and adverse events at the same time.

### Cost-effectiveness

The conduct and reporting of the cost-effectiveness analyses will follow Consolidated Health Economic Evaluation Reporting Standards (CHEERS). All costs will be expressed according to a single price year and will be converted to US$. Costs and outcomes will be discounted at 3%, with variation in sensitivity analysis. Our study team will estimate the cost per participant in SCOPE-PP versus the standard of care from baseline to 6, 12 and 15 months postpartum and relate these costs to primary outcomes in order to estimate incremental cost-effectiveness ratios (ICERs) in natural units. For this analysis, the scope of costs will include the costs to the health system of facility-based PrEP prescription, HIV counseling and testing as well as the costs of providing maternal PrEP in the community (Table 4).

**Table 4 Tab4:** SCOPE-PP Outcomes, Measures, Data Sources, and Timing (Aims 1 and 2)

Outcomes	Measures	Data Sources	Follow-up timing

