**Methods:**

Stepped Care to Optimize PrEP Effectiveness in Pregnant and Postpartum women (SCOPE-PP), is a two-stepped unblinded, individually randomized controlled trial (RCT) that aims to optimize peripartum and postpartum PrEP use by providing a stepped package of evidence-based interventions. We will enroll 650 pregnant women (> 25 weeks pregnant) who access PrEP at a busy antenatal clinic in Cape Town at the time of recruitment and follow them for 15 months. We will enroll and individually randomize pregnant women > 16 years who are not living with HIV who are either on PrEP or interested in starting PrEP during pregnancy. In step 1, we will evaluate the impact of enhanced adherence counselling and biofeedback (using urine tenofovir tests for biofeedback) and rapid PrEP collection (to reduce time required) on PrEP use in early peripartum compared to standard of care (SOC) (*n* = 325 per arm). The primary outcome is PrEP persistence per urine tenofovir levels and dried blood spots of tenofovir diphosphate (TFV-DP) after 6-months. The second step will enroll and individually randomize participants from Step 1 who discontinue taking PrEP or have poor persistence in Step 1 but want to continue PrEP. Step 2 will test the impact of enhanced counseling and biofeedback plus rapid PrEP collection compared to community PrEP delivery with HIV self-testing on PrEP use (n = up to 325 postpartum women). The primary outcome is PrEP continuation and persistence 6-months following second randomization (~ 9-months postpartum). Finally, we will estimate the cost effectiveness of SCOPE-PP vs. SOC per primary outcomes and disability-adjusted life-years (DALYs) averted in both Step 1 and 2 using micro-costing with trial- and model-based economic evaluation.

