**Randomization of pregnant women on PrEP (= > 25 weeks gestation)**			
**Baseline Study visit**	In clinic: PrEP offer, standard counseling	In clinic: PrEP offer, standard counseling	In study site (behind clinic): • Consent form • Survey • Reimbursement for time
**1 month clinic visit**	In clinic: PrEP refill and standard counseling, urine testing (no feedback)	In clinic: PrEP refill with urine testing and feedback on PrEP levels in urine	Standard monitoring No reimbursement for time
**3 month Study visit**	In clinic: PrEP refill and standard counseling, urine testing (no feedback) With standard HIV testing/HIVST	In clinic: PrEP refill with urine testing and feedback on PrEP levels in urine With standard HIV testing/HIVST	In study site: • Blood collection • Survey • Reimbursement for time
**6 month** **Study visit**	In clinic: PrEP refill and standard counseling, urine testing (no feedback) With standard HIV testing/HIVST	In clinic: PrEP refill with urine testing and feedback on PrEP levels in urine With standard HIV testing/HIVST	In study site: • Blood collection • Survey • Reimbursement for time
**If participant continues on PrEP and adherent based on urine testing, can continue in study according to following visits. If not adherent or discontinues, can participate in RCT Step 2 (LATE-PREP-P).**			
**9 month clinic visit**	In clinic: PrEP refill and standard counseling, urine testing (no feedback) With standard HIV testing/HIVST	In clinic: PrEP refill with urine testing and feedback on PrEP levels in urine With standard HIV testing/HIVST	Standard monitoring No reimbursement for time
**12 month Clinic visit**	In clinic: PrEP refill and standard counseling, urine testing (no feedback) With standard HIV testing/HIVST	In clinic: PrEP refill with urine testing and feedback on PrEP levels in urine With standard HIV testing/HIVST	Standard monitoring No reimbursement for time
**15 month Study visit**	In clinic: PrEP refill and standard counseling, urine testing (no feedback) With standard HIV testing/HIVST	In clinic: PrEP refill with urine testing and feedback on PrEP levels in urine With standard HIV testing/HIVST	In study site: • Blood collection • Survey • Reimbursement for time

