#### Outcomes

The primary outcome for Step 1 is early PrEP continuation and persistence per urine TFV at 6 months postpartum (verified post hoc via DBS analysis of TFV-DP - high persistence is defined as having levels above 2 pills per day or = > 650 fmol/punch in pregnant women and = > 950 fmol/punch in postpartum women) [31]. Secondary outcomes include:**Perfect PrEP persistence:** we will measure perfect PrEP persistence (e.g., level of objective PrEP persistence measured with DBS of TFV-DP through peripartum and postpartum period at 6 and 12 months following PrEP start) as well as “prevention-effective” [32, 33] adherence among participants, which measures PrEP use prior to (7+ days) and during times of sexual activity (using self-reported recent sexual activity). We will use benchmarked blood levels from IMPAACT 2009 results for pregnant and postpartum women as= > 650 fmol/punch in pregnant women and = > 950 fmol/punch in postpartum women [31].**HIV incidence** in participants (measured at each follow-up survey using SOC HIV tests)**Uptake of male partner HIV testing**, measured as the proportion of male partners who test (either through HIVST or standard facility-based testing), as reported by the female participantNumber of participants reporting adverse events (i.e., side effects, IPV, end of relationship)

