**Aim 1: Efficacy of SCOPE-PP (*****Primary Outcomes)***			
Efficacy of SCOPE-PP	**Perfect Persistence:** Persistence on PrEP (%, time on PrEP adherent). Perfect persistence in postpartum = > 950 fmol/punch in DBS TFV-DP), by study arm	DBS TDF-DP	RCT 1: 6 months RCT 2: 15 months postpartum
	**Prevention-Effective Persistence:** Persistence on PrEP when sexually active (in postpartum women = > 950 fmol/punch in DBS TFV-DP), by study arm	DBS TDF-DP	RCT 1: 6 months RCT 2: 15 months postpartum
	**Self-reported persistence:** self-reported measures of PrEP use and pill counts over the phone	Self-reported PrEP persistence &pill count	Quarterly
	**Secondary outcomes**: HIV incidence (maternal and infant), adverse events and IPV	RedCap clinical data	Monthly

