**Aim 2: Evaluate cost effectiveness of SCOPE-PP**			
Incremental cost of Scope-PP	Based on micro-costing, evaluate incremental cost per participant of SCOPE-PP from baseline to 6, 12 and 15 months postpartum by trial step	Quantitative surveys at each visit	RCT 1: 6 months RCT 2: 15 months postpartum
Incremental cost per improved PrEP continuation and persistence	Using trial-based cost-effectiveness analysis, evaluate incremental cost per improved PrEP continuation and persistence at 6, 12 and 15 months postpartum for SCOPE-PP (integrating step 1 and step 2 trials)	Quantitative surveys at each visit	RCT 1: 6 months RCT 2: 15 months postpartum
Incremental cost per DALY averted	Using model-based cost-utility analysis, evaluate incremental lifetime cost and DALYs averted for SCOPE-PP and assess value for money	N/A	N/A (model-based analysis)

*SCOPE-PP* Stepped care to optimize pre-exposure prophylaxis (PrEP) effectiveness in pregnant and postpartum women, *DALY* disability adjusted life year, *CFIR* Consolidated Framework for Implementation Research, *PrEP* pre-exposure prophylaxis, *HIVST* HIV self-testing, *TFV-DP* tenofovir diphosphate

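### The 15-month-postpartum cost horizon falls after the last study visit, and the 12-month dried-blood-spot outcomes have no scheduled blood draw for nearly all women

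*Protocol article*

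**What the plan says.** **Cost horizons.** The Cost-effectiveness section estimates cost per participant "from baseline to 6, 12 and 15 months postpartum" and relates it to the primary outcomes. Table 4 (Aim 2) plans to "evaluate incremental cost per improved PrEP continuation and persistence at 6, 12 and 15 months postpartum", integrating both steps. It gives the data source as "Quantitative surveys at each visit" and the timing as "RCT 1: 6 months RCT 2: 15 months postpartum". The Aim 1 rows of Table 4 also place the Step 2 DBS measures at "RCT 2: 15 months postpartum".

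**Follow-up.** The Abstract says the trial will enrol 650 pregnant women and "follow them for 15 months". Table 1 starts at randomization in pregnancy and ends with a study visit at month 15. Step 2 is entered at month 6 of Step 1 (text below Table 2) and ends at its own month 9.

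**DBS timing.** The Step 1 Outcomes section measures tenofovir diphosphate in DBS "at 6 and 12 months following PrEP start". The Data analysis section repeats 12 months for women who are not re-randomized, and for Step 2 uses DBS at 6 months after the second randomization. Table 1 lists blood collection at months 3, 6 and 15. Its row "12 month Clinic visit" carries standard monitoring only. Table 2 lists blood only at its month-9 visit.

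**The concern.** Every woman is pregnant at time zero, so a horizon counted from delivery always ends later than the same number of months counted from randomization. With follow-up fixed at 15 months from randomization, 15 months postpartum cannot be observed on schedule. A trial-based ratio reported at that horizon would rest either on costs and outcomes nobody recorded, or on month-15 data carrying the wrong label.

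The DBS problem is of the same kind. An outcome is named at a time when the schedule takes no sample, while the blood drawn at month 15 in Step 1 serves no DBS outcome named in the Step 1 Outcomes or Data analysis sections. An analysis plan cannot recover a specimen that was never collected, so this has to be settled in the schedule.

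**Working it through.** **1. Cost horizon**

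Inputs:
- Enrolment beyond 25 weeks (Step 1, Recruitment and enrolment). I use 25 weeks as the bound and 36 weeks as an illustrative late enrolment.
- Last visit: month 15 in Step 1 (Table 1); 6 + 9 = month 15 in Step 2 (Table 2).
- Gestation at delivery is not stated. I assume 40 weeks, range 37 to 42.
- Weeks per month: 52.1775 / 12 = 4.348.

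Formulas:
- Offset = (delivery week − enrolment week) / 4.348.
- Months postpartum at a visit = study month − offset.
- Study month of 15 months postpartum = 15 + offset.

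*Reproducing the plan's own figure.* The Abstract puts 6 months after the second randomization at about 9 months postpartum, and the Step 2 Outcomes section puts the same point at about 12 months of follow-up. For enrolment at 27 weeks, the offset is 13 / 4.348 = 2.99 and 12 − 2.99 = 9.01. Enrolment at 25 and 28 weeks gives 8.55 and 9.24. The plan's figure is reproduced, and it implies an offset of about 3 months. On that conversion, month 15 is about 12 months postpartum.

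*Delivery at 40 weeks:*

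| Enrolled at (weeks) | Offset (months) | Month 15 is, months postpartum | 15 months postpartum is study month | 12 months postpartum is study month |
|---|---|---|---|---|
| 25 | 3.45 | 11.55 | 18.45 | 15.45 |
| 27 | 2.99 | 12.01 | 17.99 | 14.99 |
| 32 | 1.84 | 13.16 | 16.84 | 13.84 |
| 36 | 0.92 | 14.08 | 15.92 | 12.92 |

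The shortfall at the longest horizon equals the offset: 0.92 to 3.45 months. Varying delivery from 37 to 42 weeks, month 15 is 12.24 to 11.09 months postpartum for enrolment at 25 weeks, and 14.77 to 13.62 for enrolment at 36 weeks. No combination reaches 15.

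The 12-month-postpartum point is just missed at 25 weeks (month 15.45) and lies within follow-up from about 27 weeks. The 6-month point falls at study month 6 + 0.92 = 6.92 to 6 + 3.45 = 9.45, well inside follow-up.

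**2. DBS at 12 months, Step 1**

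Blood is drawn at study months 3, 6 and 15. Twelve months after PrEP start is study month 12 − (months on PrEP before enrolment):

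| Months on PrEP before enrolment | Study month | Blood drawn? |
|---|---|---|
| 0 (starts at baseline) | 12 | No |
| 1 to 5 | 11 to 7 | No |
| 6 | 6 | Yes |
| 9 | 3 | Yes |

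For a woman starting at baseline, the nearest draws are 6 months earlier and 3 months later.

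**3. DBS at Step 2 month 6**

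This is study month 6 + 6 = 12. Table 2 makes it a service visit with standard monitoring and lists no blood. The only Step 2 follow-up draw is at its month 9, which is study month 15.

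**The case against.** **A mislabelled time origin.** The horizons 6, 12 and 15 look like follow-up months, and month 15 is the last visit in both steps, with survey and blood. A slip in the label is at least as plausible as a plan to analyse unobserved data. This stands, and it is why the correction is mostly one of wording. Nor would relabelling bias the comparison between arms: randomization makes gestation at enrolment similar by arm in expectation. What would be misstated is the horizon.

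**A different clock for Step 2.** The Step 1 primary outcome is at 6 months after randomization in the Aims but at 6 months postpartum in the Step 1 Outcomes section and Table 3. Hypothesis 2 in the Aims also speaks of 12 months postpartum. If Step 2 began at 6 months postpartum, its month-9 visit would be 15 months postpartum, which would explain the Table 4 label. But that contradicts the 15-month total follow-up, the Table 1 clock, re-randomization at month 6 of Step 1 and the Abstract's own conversion to about 9 months postpartum. It also does nothing for women who stay in Step 1. The objection shows that the time origin is unsettled; it does not rescue the text.

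**Month 12 is not empty.** A reader might infer that nothing is measured then and that the outcome is missing for every woman. The documents do not support this. Table 1 includes urine testing and a refill at month 12 in both arms. The Follow-up surveys section (four surveys, every 3 months) and Table 4 (a survey of all participants at 12 months of follow-up) conflict with Table 1, which lists no survey then. Because the outcome counts from PrEP start, a few long-term prior users could coincide with a month-6 or month-3 draw. None of these sources schedules blood at month 12.

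**Conclusion.** The point holds in a limited form: stated time points and the visit schedule do not match.

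- **Costs.** The 15-month-postpartum point is unobserved for essentially every woman, by about 0.9 to 3.5 months (enrolment at 36 to 25 weeks, delivery assumed at 40). A reader might conclude that the whole trial-based economic evaluation is unmeasurable. It is not: 6 months postpartum is reachable and 12 months mostly so.
- **DBS.** The 12-month Step 1 secondary outcome has no scheduled sample for nearly all women. Saying nearly all assumes that few were on PrEP for about 6 or 9 months before enrolment; the article gives no distribution. The same gap occurs at Step 2 month 6, where DBS is meant to verify the primary outcome.

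The delivery assumption changes the size of the shortfall, not its existence. The matter is worth correcting because it decides what can be measured, but it does not threaten the randomized comparison itself.

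**What to change.** 1. Use one time origin, months since Step 1 randomization, in the Step 1 Outcomes, Cost-effectiveness and Data analysis sections and in Table 4 (Aims 1 and 2).
2. State the trial-based cost horizons as months 6, 12 and 15 of follow-up, with the month-12 outcome based on urine tenofovir and refill data. Leave anything beyond month 15 to the model-based analysis.
3. Define the later Step 1 DBS outcome at month 15. Blood is already drawn then, and it coincides with the Step 2 month-9 draw. Moving the Step 1 draw to month 12 instead would break that alignment.
4. Reconcile Table 2 with the Step 2 Outcomes and Data analysis sections: either state the Step 2 DBS measure at its month 9, or schedule a draw at its month 6. Table 2 lists urine testing only in the counselling group, so it should also show how urine is obtained in the community group at month 6, as the urine-based primary outcome requires.
5. Make Table 1 agree with the Follow-up surveys section and Table 4 on whether a survey is done at month 12.

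Cost: items 1 to 3 are wording, with no new Step 1 visit or sample. Item 4 adds a collection only if the Step 2 month-6 draw is chosen, or if community-group urine is not already planned. The longest cost horizon becomes about 1 to 3.5 months shorter on the postpartum scale, and the later Step 1 DBS outcome moves from 12 to 15 months.
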